### Statistical methods

Primary outcome: the primary estimand of interest is the between-group difference in the proportion of patients with a nonunion at 12 months in the full trial population grouped according to their treatment allocation (treatment policy estimand). Point and interval estimates for the between-group difference will be determined from a competing risk model that incorporates death as a competing risk.

Losses to follow-up will be censored at the last study visit. If the loss to follow up for the primary outcome is > 5% overall or in either treatment group, a sensitivity analysis will be conducted using a weighted generalized estimating equation approach. Secondary repeatedly measured, continuous outcomes will be analyzed using a linear mixed-effects model with a random effect for patient nested within study center. Structural accuracy, which has 4 measures: mandibular width and projection deviation, deviation in donor bone segment lengths and angles, will be compared with O’Brien’s global test to obtain an overall assessment of the intervention on the 4 accuracy measurements. O’Brien’s test is sensitive to effects that are consistent across the multiple measures increasing power, while simultaneously lowering type 1 error rates.

### Confidentiality

All hard copy records will be stored in a locked cabinet in the PI’s office, which is only accessible by the PI and authorized members of the research team. All data will be de-identified and labelled with a study ID that is not derived by personal identifiers, such as SIN, PHN, DOB or initials. A master list that will link the participant’s name and PHN to their study ID will be recorded on a hard copy that will be stored in the PI’s office in the Otolaryngology Clinic at VGH. This data will be kept separate from the data collection forms.

### Data and safety monitoring

The Data and Safety Monitoring Committee (DSMC) will consist of a head and neck surgeon with experience in clinical trials, a biostatistician and an expert in virtual surgery. The DSMC is independent from the investigators and team members involved in the trial. The DSMC will meet bimonthly to review any adverse outcomes and complication rates, and will recommend any modifications to the TSC. The DMSC must be sufficiently satisfied with study progress and safety to approve the continuation of the study.

An interim analysis will be performed by an independent statistician after 50% of the sample size have enrolled and completed their 1-year follow up and CT scan. The statistician will report to the DSMC, which will then decide whether to continue the study based on the Peto stopping guideline (two-sided *p* < 0.001). Data collected from the semi-structured interview will be reviewed during this analysis to determine whether sex, gender or other factors affect patient participation in the trial. The TSC will use this data to change recruitment strategy as appropriate.

### Adverse events

The Common Terminology Criteria for Adverse Events (CTCAE) version 4.0 grading scale will be used to assess adverse events. For any grade 4 or 5 adverse event, the Principal Investigator and local REB will be notified, and a Serious Adverse Event form will be completed and stored on REDCap.

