### Secondary outcomes

Complication rates: These include short-term and long-term complications such as flap failure, infection, and long-term plate extrusion. Adverse events will be identified during routine follow-up, by chart review and by a structured interview with participants.Operative time, ischaemic time and length of stay will be abstracted from the patients’ medical chart.Structural reconstruction accuracy: These will be measured comparing preoperative versus postoperative CT scans using cephalometric measurements including intracondylar distance and mandibular angles.Quality of Life measurements: The University of Washington Quality of Life Questionnaire (UWQOL), MD Anderson Dysphagia Inventory (MDADI), and The General Oral Health Assessment Index (GOHAI) will be collected to be consistent with other studies in this patient population [36, 37]. The UWQOL is a well-validated instrument for this patient cohort and has been demonstrated to have strong internal consistency (Cronbach’s alpha = 0.86) and reproducibility score of > 0.9035 [38–40]. The MDADI has high internal consistency (Cronbach alpha = 0.96) and test-retest stability ranging from 0.69 to 0.8837 [40]. Functional Outcomes:
Occlusal force (bite force): will be determined using the Dental PreScale System (DPS–Fujifilm Global).Donor site morbidity: will be measured by the Lower-Limb Tasks Questionnaire (LLTQ) or the Disabilities of the Arm, Shoulder, Hand (DASH) Questionnaire, both of which have been validated for patients receiving surgery affecting these areas [41, 42]. Occlusion and jaw freedom of movement will be measured and recorded.Dental implantability will also be assessed and determined post-operatively by an independent oral surgeon, who will be blinded to the interventions on the trial [43]. 
Economic Analysis: This will be performed based on the EQ-5D-5 L survey and a health utilization questionnaire (HUQ). Non-hospital visits will be captured through the HUQ that will be administered during each data collection point. Costs of all health care encounters will be done by usual means (e.g., physician costs from Provincial fee schedules, hospital costs from hospital finance departments, drug costs from the health authority and Provincial schedules). We will examine societal costs through the HUQ which has a section on lost productivity and other ‘out-of-pocket’ costs.

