### Treatment and follow-up

Patients will have their surgery scheduled according to local practice. Those patients randomized to the VSP arm will need a minimum of 6 business days from consent to surgery to allow for the production and shipping of the surgical guides. A comparable delay in the FHS arm will not be present, however most patients wait on average 3–4 weeks between consent and surgery.

Participants will be followed during their hospital stay (on average 7–10 days) and at standard clinic intervals (1-, 6-, and 12- months post-surgery) (Table 1).

**Table 1 Tab1:** Schedule of events

Schedule of events	Enrollment			Follow-up				Close-out
	Baseline visit	Allocation	Before surgery	5 days	1 m	6 m	12 m	
Screen for eligibility	X							
Informed consent	X							
Allocation		X						
Screen for adverse events					X	X	X	
Head and neck; abdominal or leg CT scans			X (at least 6 days prior to surgery)	X			X	
Virtual surgical planning; guides 3D printed, sterilized, and shipped to participating sites			X					
Clinical Measurements (jaw mobility, bite force)	X				X	X	X	
Surveys (UW-QOL, EQ-5D-5 L, MDADI, LLTQ/DASH, GOHAI) and HUQ	X				X	X	X	
Data analysis								X
Publication								X

The patient population under study (60% squamous cell carcinoma, 10% ameloblastoma, 7.5% osteosarcoma, 15% osteoradionecrosis, and 7.5% other) have a serious illness and are largely compliant with scheduled follow-up. To maintain desired precision (power), we have incorporated a 5% loss to follow up in our sample size calculation. We anticipate 10% will die within the 1st year of surgery based on the AJCC staging manual and historical site data [52]. Deaths will be considered a competing risk to non-union in the analysis.

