## Discussion

Despite advances in surgical techniques, the morbidity associated with advanced oral cavity defects requiring reconstruction remains high, and its subsequent detrimental effects on quality of life are well documented [53]. VSP has great potential to reduce complication rates, limit morbidity, and improve functional outcomes and quality of life; however, there is no high-quality evidence to support its efficacy. As a result, VSP adoption is variable, with scepticism concerning clinical outcomes and cost-effectiveness. In Canada, three centres have already adopted this technique including Misericordia Community Hospital (Edmonton), Foothills Medical Centre (Calgary) and Montreal General Hospital. However, two of the three centres utilize commercial VSP products with significantly increased costs to the health care system. The third centre has a well-funded program that provides an in-house solution that could only be translated to other centres with significant capital cost investments in software and hardware.

The in-house VSP technology proposed in this study is open-source and can be easily adopted by other centres. The remaining centres across Canada, including those enrolled in this trial, account for over 50% of total mandibular reconstructions in the country and have not adopted VSP due to a lack of definitive evidence of its benefits and its significantly increased cost. A recent base-case analysis by Fatima et al. (2019) [54] found VSP was costlier than usual care by $7099.00 (2016 US $) per person. Furthermore, their analysis revealed higher flap loss (83/1000 vs. 77/1000) and higher rates of mandibular infection (308/1000 vs. 243/100) with VSP vs. FHS, although considerable uncertainty was associated with these estimates [54]. This contrasts various retrospective series demonstrating increased operating room efficiency and structural outcomes [27]. 

ViPMR is a multi-center phase II/III trial that aims to randomize 420 patients to two reconstructive interventions, VSP vs. FHS, in order to assess the superiority of VSP over FHS particularly as it relates to union rates at 1 year post treatment. Additional economic, structural and functional outcomes will also be collected to determine if VSP can contribute to improve outcomes for advanced oral cavity malignancies in a financially responsible manner. Results of this study will help guide Canadian health authorities and US insurance plans in terms of the adoption of VSP nation-wide.

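### The serious-event form and notification are tied to CTCAE grade 4 or 5 alone, so a complication that is serious by its consequence but graded lower triggers neither

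*Protocol article*

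**What the plan says.** In the Protocol article, the Adverse events section adopts CTCAE version 4.0 grading and then sets one threshold: "For any grade 4 or 5 adverse event, the Principal Investigator and local REB will be notified". For those same events, "a Serious Adverse Event form will be completed and stored on REDCap". No other criterion for a serious event appears, and the DSMC is not among those notified.

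Other sections bear on how events are found and reviewed:

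- Data and safety monitoring: "The DSMC will meet bimonthly to review any adverse outcomes and complication rates". The committee must also be satisfied on safety for the study to continue.
- Treatment and follow-up: "Participants will be followed during their hospital stay (on average 7–10 days"), and then "at standard clinic intervals (1-, 6-, and 12- months post-surgery"). In Table 1 the row "Screen for adverse events" is marked at 1, 6 and 12 months only.
- Secondary outcomes: loss of the flap, infection and later extrusion of the plate are collected as complications, with no grade limit. "Adverse events will be identified during routine follow-up, by chart review and by a structured interview with participants".
- Discussion: a cited base-case economic analysis found "higher flap loss (83/1000 vs. 77/1000) and higher rates of mandibular infection" with VSP. The article adds that these estimates are quite uncertain.

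**The concern.** Severity and seriousness are different properties of an event. A grade describes how intense the event is. Seriousness describes what it led to: death, threat to life, admission to hospital or a longer stay, a further operation, or lasting disability. A rule based on grade alone leaves the second property out.

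This matters here because the complications the trial lists can be serious through what follows from them, for example a lost flap that needs another operation or an infection that leads to readmission. If such an event is graded below 4, the stated rule asks for no serious-event form and no notice. It is then left to the ordinary collection of complications, whose scheduled screens are months apart after the first month. The DSMC meets far more often than that, so its complication rates for recent months may be incomplete.

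**Working it through.** The plan gives no figure for reporting delay, so there is nothing to reproduce. The check sets the stated rules side by side and takes differences of the screening times.

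**1. What triggers a serious-event form.** The only trigger in the Adverse events section is grade 4 or 5.

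- Grade 4 or 5, any consequence: form, and notice to the Principal Investigator and REB.
- Below grade 4, with readmission, longer stay, return to theatre or lasting disability: neither.
- Below grade 4, without such a consequence: neither.

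The rule treats the second and third rows alike. That is the defect.

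**2. What reaches the DSMC.** Its remit covers adverse outcomes and complication rates in general, so the grade rule is not a filter on it. But the Adverse events section sends notice only to the Principal Investigator and REB. No prompt route to the DSMC is stated there, even for grade 4 or 5.

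**3. Screening gaps.** Screening times are 1, 6 and 12 months after surgery (Table 1), with surgery at 0.

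- 1 − 0 = 1 month
- 6 − 1 = 5 months
- 12 − 6 = 6 months

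**4. Longest wait until a DSMC meeting**, if an event surfaces only at a scheduled screen: gap plus one meeting interval. The word bimonthly can be read two ways.

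- Every 2 months: 1 + 2 = 3, 5 + 2 = 7, 6 + 2 = 8 months.
- Twice a month (0.5 month): 1.5, 5.5 and 6.5 months.

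These are upper limits. An event found by chart review, in routine care or during the hospital stay arrives sooner.

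**5. Whether the interim analysis is an earlier backstop.** It is performed once half the sample has enrolled and completed 1-year follow-up. At the planned 140 patients per year, assuming steady accrual, 210 / 140 = 1.5 years, plus 1 year of follow-up = 2.5 years. By then 2.5 × 140 = 350 of 420 are randomised. Bimonthly review is therefore the timely safety check.

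**6. What cannot be sized.** The cited rates applied to 210 per arm, reading the printed 243/100 as 243/1000 (an assumption), give:

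- Infection: 0.308 × 210 = 64.7 against 0.243 × 210 = 51.0, a difference of 6.5 percentage points.
- Flap loss: 0.083 × 210 = 17.4 against 0.077 × 210 = 16.2, a difference of 0.6 points.

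These are totals over the whole trial. They are not counts of events that would be delayed or would miss a form. Turning them into such counts needs the share graded below 4, the share with a serious consequence and the onset times. The documents give none of these.

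**The case against.** The strongest reply is that the grade rule and the DSMC's information are separate matters. The rule governs notice to the Principal Investigator and REB, while the DSMC reviews adverse outcomes and complications whatever their grade. This stands. A reader might infer that the DSMC is kept from seeing events below grade 4; the documents do not say so.

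Second, Table 1 is not the only means of capture. Participants are followed in hospital, and chart review and routine follow-up are also named. This stands too, and makes 5 to 6 months a worst case for events that those routes miss. The long gaps also begin only after month 1, so they do not touch a flap lost in hospital or in the first month. A reader might want an extra screen at the day-5 assessment, but day 5 falls within the average 7 to 10 day stay and would largely duplicate in-hospital follow-up.

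Third, the cited harms are weak evidence. The flap-loss difference is 6 per 1,000 and the article itself stresses the uncertainty. Nothing in the Discussion attributes the events to the guides, so calling them device-related goes beyond the text. Nor can one say that deaths would make up most of the serious-event reports: that assumes most flap losses and infections grade below 4, and the CTCAE definitions are not reproduced.

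Fourth, an article condenses. Reporting deadlines and DSMC listings may well be in the full protocol, and their absence here is not the point. The threshold, however, is printed. The text does not contain the word only, but grade is the sole trigger it gives.

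**Conclusion.** The point holds in a limited form. The article prints a serious-event rule based on severity grade alone, and by that rule an event that is serious by consequence but graded below 4 needs no form and no notice. Alongside this, an event after month 1 that other routes miss could wait up to 5 to 6 months to be recorded, or about 5.5 to 8 months to reach a DSMC meeting, depending on how bimonthly is read.

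The first conclusion rests only on the printed text. The second assumes that the event is found only at a scheduled screen. The number of events affected in either way is unknown. The matter concerns safety oversight and does not affect the primary comparison of non-union. It merits an amendment.

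**What to change.** In the Adverse events section, define a serious event by consequence as well as by grade: death, threat to life, readmission or prolonged stay, unplanned return to theatre, or persistent disability. Have the site enter the event in REDCap when it becomes aware of it, without waiting for the next scheduled screen. Have the independent statistician, who already reports to the DSMC for the interim analysis, supply listings by arm to each bimonthly meeting, so that the blinded coordinators, assessors and trial statistician stay blinded.

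The cost is amendment wording, preparation of the listings and more serious-event forms. How many more depends on grading that the documents do not give. No new visits are needed.

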### Data storage & auditing

De-identified data will be stored on the secure online clinical database, REDCap. Access to REDCap will be granted to investigators, LSRCs, and RE. Independent from the investigators and researchers involved in the trial, the Vancouver Coastal Health Research Institute Clinical Research Unit will perform ongoing audits.

### Protocol amendments

Protocol amendments such as modifications to the eligibility criteria, outcomes, analyses will be approved by the principal investigator and will be communicated to all investigators, REBs, and trial registries.

### Dissemination

Trial results will be embargoed until information release is authorized by the principal investigator and will be communicated to the public, participants and healthcare professionals via publication and presentation within a year of study closeout. Authorship of the protocol and trial report will be decided by the principal investigator. We do not intend to use professional writers for any stage of manuscript preparation.

## Discussion

Despite advances in surgical techniques, the morbidity associated with advanced oral cavity defects requiring reconstruction remains high, and its subsequent detrimental effects on quality of life are well documented [53]. VSP has great potential to reduce complication rates, limit morbidity, and improve functional outcomes and quality of life; however, there is no high-quality evidence to support its efficacy. As a result, VSP adoption is variable, with scepticism concerning clinical outcomes and cost-effectiveness. In Canada, three centres have already adopted this technique including Misericordia Community Hospital (Edmonton), Foothills Medical Centre (Calgary) and Montreal General Hospital. However, two of the three centres utilize commercial VSP products with significantly increased costs to the health care system. The third centre has a well-funded program that provides an in-house solution that could only be translated to other centres with significant capital cost investments in software and hardware.

The in-house VSP technology proposed in this study is open-source and can be easily adopted by other centres. The remaining centres across Canada, including those enrolled in this trial, account for over 50% of total mandibular reconstructions in the country and have not adopted VSP due to a lack of definitive evidence of its benefits and its significantly increased cost. A recent base-case analysis by Fatima et al. (2019) [54] found VSP was costlier than usual care by $7099.00 (2016 US $) per person. Furthermore, their analysis revealed higher flap loss (83/1000 vs. 77/1000) and higher rates of mandibular infection (308/1000 vs. 243/100) with VSP vs. FHS, although considerable uncertainty was associated with these estimates [54]. This contrasts various retrospective series demonstrating increased operating room efficiency and structural outcomes [27]. 

ViPMR is a multi-center phase II/III trial that aims to randomize 420 patients to two reconstructive interventions, VSP vs. FHS, in order to assess the superiority of VSP over FHS particularly as it relates to union rates at 1 year post treatment. Additional economic, structural and functional outcomes will also be collected to determine if VSP can contribute to improve outcomes for advanced oral cavity malignancies in a financially responsible manner. Results of this study will help guide Canadian health authorities and US insurance plans in terms of the adoption of VSP nation-wide.

## Data Availability

No datasets were generated or analysed during the current study.
